## Materials and methods

2

### Study setting

2.1

We will recruit two cohorts of eight schools from the North and East regions of Texas to participate in this study. Texas A&M AgriLife Extension defines North and East Texas as a 44-county service area. From west to east, this region includes Cooke, Denton, and Tarrant counties – which includes the Dallas-Fort Worth metroplex – and all other Texas counties east of the Trinity River. From north to south this region includes counties along the Oklahoma border, and extends south to Jasper/Newton counties (a full list of counties can be found at agrilifeextension.tamu.edu/about-2/district-offices-regional-centers/).

Counties in the North and East Texas AgriLife regions have some of the highest rates of cardiovascular disease in the country; and the prevalence of MetS is around 9%. The average rate of cardiovascular disease in these 44 counties is 556.3 deaths per 100,000 people over 18 years of age, which is substantially higher than the average of all Texas counties (442.5 per 100,000 people) and the average of all counties in the United States (432.3 per 100,000 people) (27). The rates in these counties are also higher for deaths from heart disease (430.6 vs. 334.5 in Texas vs. 325.7 in the United States), deaths from stroke (92.14 vs. 80.1 in Texas vs. 75.7 in the United States), and preventable/avoidable deaths from cardiovascular diseases (403.4 vs. 324.6 in Texas vs. 310.3 in the United States) (27). Similarly, these counties also have a higher average prevalence of cardiovascular disease risk factors than the average of other Texas counties, including for high blood pressure (39.1% vs. 37.4% in Texas), high cholesterol (40.0% vs. 39.6% in Texas), diabetes (8.2% vs. 7.9% in Texas), obesity (23.1% vs. 21.4%) leisure time physical inactivity (17.7% vs. 16.1%) and smoking (18.3% vs. 17.0%) (27).

### Study design

2.2

We will examine how three discrete implementation strategies affect important implementation and cardiovascular disease outcomes using the Multiphase Optimization STrategy (MOST) framework and a cluster randomized factorial design. The cluster randomized full factorial design allows us to calculate effect estimates of each individual strategy, as well as all combinations of strategies (e.g., antagonistic or synergistic interactions between components). Using the MOST framework allows us to optimize implementation support strategies for schools in three iterative phases – (1) screening, (2) refinement, and (3) testing. In the screening phase, we develop and select each discrete strategy to be optimized. In the refining phase, we decide the optimal dosage and combination of strategies by conducting the factorial experiment(s) and calculating the main effect of each strategy and interaction effects between strategies. In the testing phase, the optimal dosage and combination of strategies will be evaluated through a randomized controlled trial. This study protocol includes the first two phases of MOST in preparation for a future randomized controlled trial. The trial is reported following consort guidelines for a randomized trial, including extensions for clustered and factorial designs.

### Study eligibility

2.3

For a school to be eligible to participate, it must be a public elementary school located in North or East Texas implementing the HSRC initiative (28, 29). For implementers to be eligible to participate, they must be 18 years old or older, be able to read and communicate in English, and be affiliated with a school that is eligible to participate.

For students to be eligible to participate in the study, they must be enrolled in the 5th or 6th grade, be at least 10 years old, have no known motor or cognitive impairments or other health conditions that would prevent them from completing assessments. The age of 10-years-old was selected because diagnostic criteria for MetS do not exist for children under that age (3). Students who have reported ever losing consciousness from pain or at the sight of blood will also be excluded to assist in diminishing the risk of fainting during assessments. Students must also be able to speak, read and write in English. For parents to be eligible to participate, they must be 18 years old or older with children enrolled in the participating schools and grade levels.

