#### Healthy school recognized campus (HSRC) initiative

2.4.2

For this study, all schools will agree to participate in the HSRC initiative. The HSRC initiative promotes the delivery of physical activity and healthy eating programs by bundling AgriLife Extension’s school- and research-based programs. For a school to be recognized as a HSRC, they are required to host a school-wide walking challenge to increase students’ physical activity (i.e., Walk Across Texas), at least one other AgriLife Extension program for students, and at least one AgriLife Extension program for adults (examples in Table 1; full list of programs found at https://texas4h-hsrc.com/). Including both interventions for students and their caretakers (i.e., teachers or parents) is also a benefit of this bundled approach, as interventions that address more than one level of the ecological model (e.g., intrapersonal, interpersonal, organizational) can be more effective than single level interventions (30–32). Programs are delivered by one or more Extension agents (i.e., health educators) in the county where the school is located (33, 34), and once the initiative’s requirements are complete, schools receive recognition via a banner and/or at a local school meeting (e.g., school board, school health advisory council).

**Table 1 tab1:** Examples of healthy school recognized campus’ research-based programs.

Program	Description	Research
Youth		
Walk Across Texas! (Youth) (69, 70)	8-week program designed to help youth across Texas establish the habit of regular physical activity using a fun and motivating team approach.	- Doubled the number of steps taken over the course of the program. - Increased the amount of time that students were active with their parents. - Decreased BMI percentile.
Learn Grow Eat and Go! (70, 71)	10-week program that teaches students about gardening, healthy eating, and being active.	- Increased the number of vegetables tasted, vegetable preferences, and nutrition knowledge. - Decreased BMI percentile.
Choose Health: Food, Fun and Fitness (72–74)	6-session program that encourages healthy eating and fitness through hands-on activities and experiential education.	- Improved overall dietary intake, vegetable intake, fruit intake. - Reduced soda/fast food intake. - Read nutrition labels and share about healthy eating with families more often. - More likely to try new food. -Increased frequency of doing physical activities.

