#### School recruitment

2.4.4

We will work with Texas A&M AgriLife Extension agents to identify schools that may be interested in participating in the study. Specifically, schools that have previously participated in AgriLife’s physical activity or nutrition programs in the past, or that have recently expressed interest in receiving school-based health programs, will be contacted. We will also share information about HSRC with eligible schools via email, at school health conferences, or at events where school staff are present. Schools that agree to participate will sign a memorandum of understanding and a site authorization that permits the conduct of research on the school campus. Schools will also complete an application for the HSRC initiative. The application lists the initial AgriLife programs that schools can choose to complete during the next year; however, schools can change their programs at any point throughout the school year.

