#### Participant recruitment

2.4.5

We aim to recruit about 20 parents (320 total), 20 students (320 total), and 10 HSRC implementers (160 total) at each school (two cohorts of *n* = 8 schools) enrolled in the study. We will share recruiting materials online (e.g., email) and in-person (e.g., back-to-school events, student drop-off and pickup) to provide details about the study. Parents agreeing to participate will complete the consent form for their child and themselves, a short survey at pre- and post-intervention, and they will be compensated with a $10 gift card at each time point. The research team will meet in-person with children who have received signed parental consent to explain the study and answer any questions. Children will sign an assent form before participating in a survey and biometrics assessment at pre- and post-intervention. They will also receive an item worth $10–$15 (e.g., t-shirt, water bottle, active toy) for each data collection timepoint (pre- and post-intervention). Children who do not agree to participate in the study will still be allowed to participate in HSRC programs. HSRC implementers (e.g., Extension agents, school staff, administrators) will complete a consent form agreeing to participate, a survey pre- and post-intervention, and interviews following the intervention. They will be compensated with a $20 gift card for each survey and $50 for the interview.

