#### Randomization

2.4.6

In each of the two cohorts, schools will be randomized to one of eight experimental conditions and will receive a different combination of implementation strategies (Table 2). In each school year, four schools will receive each implementation strategy, and four schools will not (all schools will receive the website as a constant implementation strategy). Schools and data collectors will be blinded to randomized conditions until a school completes data collection. An interim analysis (following processes outlined below) will be conducted between the two cohorts to determine if implementation strategies should be removed and/or replaced, as well as if any of the current implementation strategies should be modified.

**Table 2 tab2:** Randomized experimental conditions for this study.

Experimental condition	Constant	Factor 1	Factor 2	Factor 3
1	Website/TEKS alignment	None	None	None
2	Website/TEKS alignment	None	None	Enhanced engagement opportunities
3	Website/TEKS alignment	None	School-to-school mentoring	None
4	Website/TEKS alignment	None	School-to-school mentoring	Enhanced engagement opportunities
5	Website/TEKS alignment	Additional resources	None	None
6	Website/TEKS alignment	Additional resources	None	Enhanced engagement opportunities
7	Website/TEKS alignment	Additional resources	School-to-school mentoring	None
8	Website/TEKS alignment	Additional resources	School-to-school mentoring	Enhanced engagement opportunities

Each of the 8 conditions will be randomized one time per cohort.

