##### School-to-school mentoring

2.4.7.2

We define the school-to-school mentoring strategy as the research team facilitating connections between schools that are implementing HSRC at the same time as one another to provide a support system and technical assistance to improve implementation outcomes (i.e., acceptability, appropriateness, feasibility) – a recommendation based on qualitative interviews and focus groups. The main components of this strategy will be: (1) an introductory email, (2) monthly meetings, (3) a private Facebook group, and (4) quarterly newsletters. Immediately following randomization, participating schools will receive an introductory email welcoming them to the school-to-school mentoring program and informing them about its components (e.g., the Facebook group, newsletters). Starting around November (1–2 months into the implementation process), the research team will host monthly virtual meetings with implementers to discuss the programs being completed and successes and barriers to program implementation. At the first meeting, implementers will be invited to join a private Facebook group, which will serve as a hub for HSRC program implementers to discuss ideas, share insights on their implementation process, and seek advice outside of the group meetings. Within the Facebook group, the research team will post prompts periodically to foster engagement with the page. Finally, schools will receive quarterly newsletters designed by the research team (up to four times during the year), which will include the following elements: (1) a previously recognized HSRC school, (2) links to helpful resources for program implementation, (3) a spotlighted HSRC program, (4) a calendar of local county health-focused events, and (5) information on AgriLife Extension and its agents.

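### Nothing in the school eligibility or randomization rules keeps two schools with the same Extension agent out of one cohort, so mentoring could reach a school randomized not to receive it

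*Protocol article*

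**What the plan says.** All references are to the protocol article.

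- **Entry rule (2.3).** The criterion for schools reads: "For a school to be eligible to participate, it must be a public elementary school located in North or East Texas implementing the HSRC initiative". No condition concerns the agent or the county.
- **Delivery (2.4.2).** "Programs are delivered by one or more Extension agents (i.e., health educators) in the county where the school is located".
- **Recruitment (2.4.4).** Candidate schools are found through agents: "We will work with Texas A&M AgriLife Extension agents to identify schools that may be interested in participating in the study".
- **Who is an implementer (2.4.5).** "HSRC implementers (e.g., Extension agents, school staff, administrators) will complete a consent form". Agents are therefore implementers.
- **Mentoring (2.4.7.2).** It is aimed largely at implementers: "the research team will host monthly virtual meetings with implementers to discuss the programs being completed and successes and barriers to program implementation". A private Facebook group for implementers, an introductory email and newsletters complete it.
- **Resources (2.4.7.1).** The $2,000 incentive budget is given to the Extension agent, and the text describes the agent as the one randomized to it.
- **Allocation (2.4.6 and Table 2).** Schools are randomized. "Each of the 8 conditions will be randomized one time per cohort". Four schools per cohort receive each strategy and four do not.
- **Analysis (2.6.1).** School is the only clustering variable named. Effect estimates for each strategy guide which components are kept, and an interim analysis after the first cohort may lead to strategies being removed, replaced or modified.

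**The concern.** The randomized unit (the school) is not the unit that delivers the programs or receives part of the strategies (the agent). An agent who serves one mentored and one non-mentored school in the same year cannot set aside what was learned in the mentoring meetings when working in the second school. Section 2.4.7.1 raises a similar problem for the resource budget, because the agent holds it.

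Two things are at stake. First, carry-over pulls the contrast toward zero, so a useful strategy could look weak when components are selected. Analysis cannot undo this afterwards. Second, two schools with a common deliverer are not independent. The primary dose outcome is built from sessions that the agent delivers, yet the plan treats each school as its own cluster.

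**Working it through.** **1. The plan's own layout.** Table 2 is a 2×2×2 factorial with 8 conditions, each used once per cohort of 8. Each factor is present in 4 conditions and absent in 4. This reproduces the stated 4 vs 4 per strategy.

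**2. What a shared agent means within a cohort.** Eight schools form 8×7/2 = 28 pairs. No two schools have the same condition, so all 28 pairs differ on at least one strategy. For any single factor, the pairs that differ number 4×4 = 16.

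| Pair differs on | Pairs | Share |
|---|---|---|
| At least one strategy | 28 of 28 | 100% |
| Mentoring | 16 of 28 | 57% |
| Resources | 16 of 28 | 57% |

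The design contains no pair for which a shared agent spans identical conditions.

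**3. Effect on the contrast.** Let k of the 4 control schools receive a fraction s of the mentoring effect, and assume the effect is the same in every school. The expected contrast, as a share of the true effect, is 1 − k·s/4.

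- k = 1, s = 1: 1 − 1/4 = 75%
- k = 1, s = 0.5: 1 − 0.5/4 = 87.5%
- k = 2, s = 1: 1 − 2/4 = 50%

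If both cohorts are pooled (8 vs 8), one fully affected control school leaves 1 − 1/8 = 87.5%.

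**4. How likely sharing is.** The article gives no figure, so this step rests on an assumption: schools fall at random over m equal agent areas, with one agent each. The chance of at least one shared agent among 8 schools is 1 − ∏(1 − i/m), for i = 0 to 7. The chance that a mentored and a non-mentored school share an agent is approximately 1 − (1 − 1/m)^16, treating the 16 such pairs as independent.

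| m | Source of m | Any shared agent | Mentored and non-mentored school share |
|---|---|---|---|
| 44 | One agent area per county (44 counties, section 2.1) | 49% | 31% |
| 88 | Two per county (illustrative) | 28% | 17% |
| 158 | 44 × 900/250 (educators per office, section 2.4.1) | 16% | 10% |

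The last row is generous, since not every educator need deliver these programs in schools. Recruitment through agents would raise all three rows if keen agents put forward more than one school.

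**5. Feasibility.** "We will recruit two cohorts of eight schools from the North and East regions of Texas to participate in this study". Eight schools per cohort, drawn from 44 counties, leave room for a different agent at each school.

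**6. Fallback allocation.** With one shared-agent pair, requiring the same mentoring level keeps 28 − 16 = 12 of 28 possible condition pairs. Of the 8! = 40,320 allocations, 40,320 × 12/28 = 17,280 remain. At each mentoring level there are 4 conditions and 6 pairs, and 4 of the 6 (67%) differ on resources. Requiring the same resources level as well leaves 4 of 28 pairs, which differ on engagement only, and 5,760 allocations.

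**The case against.** The strongest objection is that this argues from silence. The article nowhere says that any agent serves two study schools, counties may have several agents, and a fuller protocol could contain a separation rule. That is fair, and the point is limited to what the printed rules permit. It still concerns a stated entry rule and a stated randomization unit, and section 2.4.7.1 itself blurs which unit is randomized.

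The dilution can also be challenged. About 10 implementers per school are sought, and the introductory email and newsletters go to schools, so one agent is likely to pass on only part of mentoring. This stands: 25% per school is an upper bound. It is also true that the study is declared not fully powered and that no interim cut-off is given, so no particular wrong decision can be shown.

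Three stronger readings are tempting, and the text does not support them:

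- **Agents carry the contests across.** Section 2.4.7.3 describes students and school staff as taking part and the principal as choosing the goal prizes. It gives agents no role in running the contests.
- **Sharing is nearly certain across the trial.** Over 16 schools and 44 areas the same formula gives 96%, but it counts any sharing in either cohort or between cohorts. Of the 8×8 = 64 cross-cohort condition pairings, only 16 (25%) go from mentored to non-mentored, and these involve remembered learning, not concurrent exposure.
- **Agents from the first cohort should be barred from the second.** Six of the eight conditions include mentoring or contests, so a bar on agents exposed to either would affect the agents of six of eight schools. Recruitment depends on agents, so this would not be cheap.

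**Conclusion.** The concern holds as a gap in the design rules, not as demonstrated contamination. The printed rules allow a shared agent within a cohort, and the one-school-per-condition layout guarantees that such a pair differs on some strategy (on mentoring in 57% of possible pairs). The expected loss in a cohort's mentoring contrast is at most 25% per affected control school, under full carry-over and a common effect. The chance of any sharing in a cohort, about 16% to 49%, depends entirely on the assumed random spread and number of agents per county. The resource budget is exposed in a similar way as long as section 2.4.7.1 places it with the agent. The change is worth making because it is cheap before randomization and the bias cannot be removed later.

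**What to change.** 1. Add to section 2.3 that, within a cohort, no two schools are served by the same Extension agent. Check this before randomization, for example when the school's application is received.
2. If this cannot be met, restrict the randomization in section 2.4.6 so that schools sharing an agent get the same mentoring level, drawing at random from the permitted allocations. Such a pair must then differ on resources or engagement. If the budget stays with the agent, the pair can be matched on resources too.
3. Record any shared agent. Repeat the analysis in section 2.6.1 with agent instead of school as the cluster, as a sensitivity check.
4. Reconcile sections 2.4.6 and 2.4.7.1 on whether the school or the agent is randomized to the resource budget.
5. Across cohorts, record which strategies each agent met in the first cohort and examine this in a sensitivity analysis. Do not exclude those agents.

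The cost is some recruitment flexibility: an interested second school of the same agent may be turned away or, under the fallback, fewer allocations are available (17,280 instead of 40,320 for one shared pair). The 4 vs 4 layout per strategy is unchanged.

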### Procedure

2.4

#### Texas A&M AgriLife Extension

2.4.1

Texas A&M AgriLife Extension is an education agency that provides programs, tools, and resources on a local and statewide level. AgriLife Extension has 250 offices (one in almost every Texas county), 900 extension educators, and a network of almost 100,000 volunteers that support the delivery of programs. Extension agents within the Family and Community Health and 4-H Youth Development units aim to help Texans better their lives through science-based educational programs designed to improve the overall health and wellness of individuals, families, and communities. Agents deliver programs in local communities (e.g., worksites, recreation centers, community events, military bases) as well as within local schools. Within schools, programs can either be delivered ad-hoc (i.e., schools choose one or more programs) or as part of the HSRC initiative.

#### Healthy school recognized campus (HSRC) initiative

2.4.2

For this study, all schools will agree to participate in the HSRC initiative. The HSRC initiative promotes the delivery of physical activity and healthy eating programs by bundling AgriLife Extension’s school- and research-based programs. For a school to be recognized as a HSRC, they are required to host a school-wide walking challenge to increase students’ physical activity (i.e., Walk Across Texas), at least one other AgriLife Extension program for students, and at least one AgriLife Extension program for adults (examples in Table 1; full list of programs found at https://texas4h-hsrc.com/). Including both interventions for students and their caretakers (i.e., teachers or parents) is also a benefit of this bundled approach, as interventions that address more than one level of the ecological model (e.g., intrapersonal, interpersonal, organizational) can be more effective than single level interventions (30–32). Programs are delivered by one or more Extension agents (i.e., health educators) in the county where the school is located (33, 34), and once the initiative’s requirements are complete, schools receive recognition via a banner and/or at a local school meeting (e.g., school board, school health advisory council).

**Table 1 tab1:** Examples of healthy school recognized campus’ research-based programs.

Program	Description	Research
Youth		
Walk Across Texas! (Youth) (69, 70)	8-week program designed to help youth across Texas establish the habit of regular physical activity using a fun and motivating team approach.	- Doubled the number of steps taken over the course of the program. - Increased the amount of time that students were active with their parents. - Decreased BMI percentile.
Learn Grow Eat and Go! (70, 71)	10-week program that teaches students about gardening, healthy eating, and being active.	- Increased the number of vegetables tasted, vegetable preferences, and nutrition knowledge. - Decreased BMI percentile.
Choose Health: Food, Fun and Fitness (72–74)	6-session program that encourages healthy eating and fitness through hands-on activities and experiential education.	- Improved overall dietary intake, vegetable intake, fruit intake. - Reduced soda/fast food intake. - Read nutrition labels and share about healthy eating with families more often. - More likely to try new food. -Increased frequency of doing physical activities.
Color Me Healthy (75, 76)	9-week curriculum extension that focuses on healthy eating and physical activity via coloring, hands-on learning, and music to help children engage with their senses.	- Increased fruit and vegetable consumption - Increased students’ knowledge of healthy eating, knowledge about physical activity, and physical activity during the school day.
Play Streets (77–79)	Series of 1-day events with various activity stations that promote safe, fun, and active play.	- Encouraged physical activity participation - Provided a safe space for outdoor play - Fostered social interaction and community connection
Adult		
Walk Across Texas! (Adult) (80)	8-week program designed to help Texans establish the habit of regular physical activity using a fun and motivating team approach.	- Increased number of miles walked per week. - Decreased leisure time sitting.
Cooking Well with Diabetes (81)	3 to 4 lesson workshops that build skills toward planning, preparing, and cooking healthy meals.	- Increase fruit and vegetable intake and the use of healthy cooking methods (e.g., baking, broiling, grilling). - Decreased sugar-sweetened beverage intake.
Maintain No Gain (82)	6-week holiday challenge to help adults maintain their current weight between Thanksgiving and New Years. Weekly weigh-ins and exercise challenges are provided.	- A majority (~80%) of participants maintained or improved their weight status during the program.

